### Non-operative treatment of displaced fractures

Non-operative management of proximal humerus fractures with a period of immobilization and progressive physiotherapy is a simple, noninvasive and readily available treatment option. In a systematic review of non-operative management, Iyengar et al. [9] evaluated 12 studies (*n* = 650) [10–21], with a mean age of 65.0 years and a mean follow-up of 3.8 years (range of 1–10 years). Based on the Neer classification [22], there were 49% undisplaced or one-part (*n* = 317), 25% two-part (*n* = 165), 21% three-part (*n* = 137), and 5% four-part (*n* = 31) fractures. Although variable, all treatment protocols included a period of sling immobilization followed by progressive mobilization as tolerated. The mean rate of radiographic union was 98% (range 93–100%). Various functional outcome scores were used; with 6 studies (*n* = 272) [10, 12, 14, 19–21] showing a weighted mean Constant score of 74 (range 55–81) corresponding to a “fair” outcome. Across all studies, a 13% complication rate was reported, with varus malunion being the most common (*n* = 44 or 7%). Proximal humerus avascular necrosis was found to be uncommon (*n* = 13 or 2%) [9]. In the largest included trial, Hanson et al. reported the functional outcomes of non-operative management through a prospective evaluation of 160 patients, with 124 patients having complete 1-year follow-up. Nearly half (53.1%) were undisplaced fractures. The average Constant score was 74.3 with a mean difference between the injured and contralateral shoulder of 8.2. They found an estimated median time to definitive union of 14 weeks, and a 7% risk of delayed or nonunion. Four patients went on to require surgical fixation and 5 patients underwent arthroscopic decompression, with an eventual operation rate of 5.6% [12]. With a large focus on undisplaced fractures, these studies highlight that non-operative management of proximal humerus fractures can lead to satisfactory functional outcomes with modest complication rates. In a report of non-operative management of displaced proximal humerus fractures, Yuksel et al. reported a mean Constant score of 61.3 (*n* = 18, eight 3-part and ten 4-part; mean age of 68.2 years; mean follow-up of 3.3 years), with nonunion and osteonecrosis detected in 27.8% (*n* = 5) [23].

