### Secondary objectives

A.Is there a difference between non-operative management and locking plate surgical fixation of low-energy displaced three- and four-part proximal humerus fractures in the elderly population based on the ASES functional outcome score [47], the short form Patient Reported Outcomes Measurement Information System (PROMIS) upper extremity score [48], the International Physical Activity Questionnaire (IPAQ) for the elderly [49], and the EuroQol EQ-5D-5 L Health Questionnaire Quality of Life (QoL) functional outcome score [50] over a 2-year follow-up period? What is the incidence of complications of non-operative management and locking plate surgical fixation of low-energy displaced three- and four-part proximal humerus fractures in the elderly population based on infection, nerve injury, intra-articular screw penetration and bleeding (hematoma), reoperation rate, or hospital readmission over a 2-year follow-up periodB.Does a difference exist between non-operative management and locking plate surgical fixation of low-energy displaced three- and four-part proximal humerus fractures in the elderly population based on radiographic outcomes including time to union, non-union, malunion, and joint arthrosis?C.Does the degree of initial displacement or angulation of the fracture fragments correlate with final functional outcome measures?D.Does the quality of the surgical reduction correlate with final functional outcome measures?

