### Secondary outcome measures

#### Classification, displacement, angulation and quality of reduction

Pre-operative plain films will include a true AP, axillary, and Y-lateral view. Post-injury radiographs including true AP, axillary views and y-lateral views will be obtained at the first post-operative visit (or 2 weeks post immobilization in the non-operative treatment arm), 6 weeks and 3, 6, 12 and 24 months following surgery. A standard computed tomography (CT) scan of the shoulder (pre operatively in all patients and immediately post-operatively in operative treated patients) will be conducted to ensure correct determination of the true nature of the fracture (3 or 4 part fracture as per the Neer [22], the OTA/AO [54] and the Hertel [55] classifications) as well as the degree of angulation and displacement of the fracture fragments. As per the Neer [22] classification, a “part” will be defined as displacement greater than 1 cm or angulation greater than 45 degrees. The OTA/AO classification [54] will also be determined on the pre-operative CT scans and classified as type A, B or C. The Hertel classification is based on a binary descriptive system that describes five basic fracture planes and twelve fracture patterns between the head, lesser tuberosity, greater tuberosity and the shaft components [55]. Pre-operative and post-operative (in the ORIF group) CT scans will be reformatted along standardized planes to determine fracture fragment position and angulation. The neck- shaft angle will be defined as the angle between the proximal humeral metadiaphysis to a line perpendicular to a line denoting the articular margin, as described by Court-Brown et al. [56]. Adequate neck-shaft reduction will be classified as a neck-shaft angle between 120 and 140 degrees. Angles below 120 and above 140 degrees will be classified as varus and valgus malunions, respectively. The plate position will be referenced with regard to the bicipital groove and the tip of the greater tuberosity on CT scan. Proper plate position will be classified as posterior to the bicipital groove and 5–8 mm below the tip of the greater tuberosity. The proximal humerus neck-shaft angle, head alignment, fracture reduction, and the hardware position will be recorded on standardized forms. We do not expect further imaging will be required.

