#### Other radiographic outcomes

Plain x-rays evaluated by an MSK radiologist will be used to determine the presence of non-union, malunion, fracture alignment, joint arthrosis and osteopenia. For the purposes of our study, nonunions will be defined as fractures that have not healed in 3 months or those with non-progressive callus formation on 3 consecutive monthly xrays [57–61]. The pre-operative films will be used to measure baseline cortical thickness of the proximal humerus on the AP shoulder view and will allow estimation of osteopenia as described by Mather et al. [62] and a baseline and final osteoarthritis grade will be determined by the method of Weinstein et al. [63].

Complications including infection, nerve injury, bleeding, intra-articular screw penetration (hardware failure), reoperation rates and hospital re-admission rates will be assessed and recorded at all follow-up visits.

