### Secondary objective analysis

A.ANOVAs will be used to compare the following two-year outcome measures between the two groups: ASES, EQ-5D-5 L, PROMIS and IPAQ. In addition, the incidence proportion of complications will be derived for each group, and a comparison of the two groups will be conducted for re-operation, infection, nerve injury, hematoma, hospital readmission, and intra-articular screw penetration using a chi-square analysis. Logistic regression modeling will be used to account for variables demonstrating group imbalance.B.The incidence of malunion, non-union, and osteoarthritis will be compared between groups using chi-square statistics (and odds ratios). Time to union will be determined with Kaplan-Meier curves with a log rank test for group comparisons.C.The degree of association between the degree of displacement and angulation of the fracture fragments and the Constant score will be determined. Multivariable regression analysis will be carried out to determine if an association exists between fracture angle and the degree of displacement (independent variables), and functional outcomes using the Constant score (dependent variable). If such an association is identified, area under the curve plots will be used to determine at what degree of angulation or displacement a particular treatment is indicated.D.The degree of association between the quality of surgical reduction [degree of displacement/angulation] of the fragments based on post-operative CT scan and the Constant functional outcome measure will be determined in the surgical group using a multivariable regression analysis.

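### Time to union is known only to lie between scheduled films, yet the plan uses ordinary Kaplan-Meier and log-rank and does not secure one time origin and film schedule for both arms

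*Protocol article*

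**What the plan says.** Secondary objective B of the protocol article asks whether the arms differ "based on radiographic outcomes including time to union, non-union, malunion, and joint arthrosis". Part B of *Secondary objective analysis* fixes the method: "Time to union will be determined with Kaplan-Meier curves with a log rank test for group comparisons". It does not mention interval censoring.

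The film schedule stands under *Classification, displacement, angulation and quality of reduction*. The first film is at the "first post-operative visit (or 2 weeks post immobilization in the non-operative treatment arm"), and the later ones are at "6 weeks and 3, 6, 12 and 24 months following surgery". The same section adds: "We do not expect further imaging will be required". *Other radiographic outcomes* says how healing is judged: "Plain x-rays evaluated by an MSK radiologist will be used to determine the presence of non-union, malunion, fracture alignment, joint arthrosis and osteopenia". It also says that "nonunions will be defined as fractures that have not healed in 3 months or those with non-progressive callus formation on 3 consecutive monthly xrays".

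The only time-to-union figure in the document is in the Background, where a cited non-operative cohort had an "estimated median time to definitive union of 14 weeks". In that cohort 53.1% of fractures were undisplaced. The protocol does not adopt the figure as an assumption for either arm.

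**The concern.** Healing is a continuous process observed at a few fixed dates. If a film shows no union and the next one does, union happened somewhere between them. Ordinary Kaplan-Meier takes the date of the second film as the event time. The curve then moves only at film dates, and any healing time read from it is a visit date.

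The second issue is the comparison between arms. A log-rank test on film dates compares healing only if both arms are filmed at the same times from the same origin. Otherwise it partly compares visit schedules. Here the schedule is written in terms that differ by arm. At stake is a stated secondary comparison, which could show a difference in healing that comes only from when the films were taken.

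**Working it through.** The protocol gives no sample size, power or median for time to union, so there is no planned figure to reproduce.

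**1. Film dates in weeks.** One month is 365.25 / 12 / 7 = 4.348 weeks. The first film is taken as week 2 (an assumption, since its wording differs by arm).

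| Film | Week | Gap from previous film (weeks) |
|---|---|---|
| first | 2 | – |
| 6 weeks | 6 | 4.0 |
| 3 months | 13.0 | 7.0 |
| 6 months | 26.1 | 13.0 |
| 12 months | 52.2 | 26.1 |
| 24 months | 104.4 | 52.2 |

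**2. What the Kaplan-Meier median becomes.** With complete follow-up, the curve at a film date is the share not yet united at that film. The median is the first film by which at least half have united. For Weibull healing times with true median m and shape k, the share not united at week t is S(t) = exp(−ln 2 × (t/m)^k).

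- m = 14, k = 2, t = 13.04: (13.04/14)² = 0.868, and S = exp(−0.693 × 0.868) = 0.548, so 45.2% are united.
- The same at t = 26.09: (26.09/14)² = 3.473, and S = exp(−2.407) = 0.090, so 91.0% are united.
- The 50% point is therefore first passed at the 6-month film. The reading is 26.1 weeks, about 12 weeks late.

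For shapes 1, 2 and 3, every tested true median from 8 to 13 weeks reads as 13.0, and every one from 14 to 24 weeks reads as 26.1.

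Sampling variation matters near the boundary. The simulation used shape 2 and 64 per arm, which is the planned 160 less 20% loss (160 × 0.8 / 2 = 64). An arm with a true median of 14 weeks read 26.1 in about 74% of runs, 13.0 in about 18%, and midway in the rest.

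**3. Log-rank test when both arms share schedule and origin** (64 per arm, 1,000 runs, no dropout).

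| True medians (weeks) | Shape | Rejection, exact times | Rejection, film dates |
|---|---|---|---|
| 14 v 14 | 2 | 0.056 | 0.059 |
| 14 v 12 | 2 | 0.41 | 0.31 |
| 14 v 11 | 2 | 0.79 | 0.64 |
| 14 v 18 | 2 | 0.79 | 0.68 |
| 14 v 12 | 3 | 0.74 | 0.47 |

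Type I error holds, and power falls for modest differences.

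**4. Log-rank test when one arm's films are later.** *Randomization and blinding* schedules surgery within 7 days of injury, so films counted from surgery can fall up to a week later from injury than films counted from injury. (*Participants* instead counts the 7 days from presentation; the two statements need to be reconciled.) Healing was set identical in both arms (shapes 1.5 to 3, medians 12 and 14 weeks, 64 per arm), with ORIF films one week later throughout:

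- Common schedule: false rejection in 4% to 7% of runs.
- One-week offset: 63% to 99% over two separate sets of runs.
- One-week offset with visits also varying by ±1 week: 35% to 87%.

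The effect is large because unions cluster at films. With m = 14 and k = 2, the share first seen united is 45.2% − 12.0% = 33.2% at the 3-month film and 91.0% − 45.2% = 45.8% at the 6-month film. When one arm's cluster is recorded a week earlier, all of those events occur while the other arm's healed patients still count as ununited and at risk.

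**5. Related conflict.** The non-union definition refers to monthly films, which the schedule does not provide. Its first clause would also cover anyone unhealed at the 3-month film. At a true median of 14 weeks that is 52% to 57% of patients (shapes 1 to 3).

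**The case against.** The strongest reply is that the plan answers the between-arm question with a log-rank test and never mentions a median. Under a shared schedule that test is valid. The Kaplan-Meier values at the film dates are then simply the proportions united at those films, and a Turnbull estimate gives the same values there. This stands. It also means that an interval-censored method cannot restore information that the spacing of films never collected.

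A reader might infer more than the documents support:

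- **That 14 weeks is this trial's expected median.** It is a result from one cited non-operative cohort, about half undisplaced. This trial enrols displaced 3- and 4-part fractures and plates one arm. Visit-date readings arise at any median; only the jump from 13 to 26 weeks needs a value near 13.
- **That films are up to 6 months apart around that time.** The adjacent gaps are 7 and 13 weeks. Gaps of 6 months or more begin only after the 6-month film.
- **That the planned analysis would hide a large difference or invent one from a trivial one.** This is true of the medians but not of the test. Under a shared schedule, true medians of 14 v 25 weeks both read 26, yet the log-rank test rejects in 99% to 100% of runs. Medians of 12.9 v 13.5 weeks read 13 v 26, yet it rejects in only 6% to 9%.

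Missed visits are mitigated by the rescheduling and telephone calls under *Compliance and loss of follow-up*. The mailed questionnaires used as a last resort supply no film.

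The reply depends on a shared schedule and origin, and the text does not secure these. It times the first film differently by arm and dates later films from an operation that one arm does not have, whereas *Outcome measures* dates the functional scores from injury.

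**Conclusion.** The point holds in a limited form. Time to union is interval-censored, and the named method treats it as exactly observed, so any healing time read from the curve will be a visit date. At a true median of 14 weeks the expected reading is about 12 weeks too late.

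The log-rank test is not invalid in itself. With one origin and one film schedule it keeps its size and loses some power. It becomes unreliable if film timing differs systematically by arm, which the current wording permits but does not prescribe. The false-rejection figures of 63% to 99%, or 35% to 87% with visit variation, rest on an assumed one-week offset, Weibull healing times, 64 per arm and no dropout. They show what could happen and do not predict what will.

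This is one of several radiographic outcomes under a secondary objective, and the primary analysis is untouched. It is a cheap and worthwhile improvement.

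**What to change.** In part B of *Secondary objective analysis*:

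- Treat union as interval-censored between the last film without union and the first film with it. Use actual film dates, counted from one time origin that exists in both arms.
- Estimate the curves by Turnbull's method, and compare the arms with an interval-censored log-rank test or an interval-censored regression model.
- Report the proportion united at the 3-, 6- and 12-month films by arm as the main description, and do not interpret a Kaplan-Meier median in weeks.

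In the film schedule, state the origin and visit windows in terms that apply to both arms. Reconcile the non-union definition with the films actually scheduled.

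The cost is wording and slightly more analysis work, using film dates that the trial will have. No extra visit, film or patient is needed. The downside is wider intervals around healing time, and the power lost to the spacing of films is not recovered.

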### Purpose and hypothesis

The main purpose of this trial is to determine whether or not a functional difference exists between operative and nonoperative management of low-energy displaced three- and four-part proximal humerus fractures as measured by the Constant, (PROMIS) upper extremity score, the International Physical Activity Questionnaire (IPAQ) for the elderly, and the EuroQol EQ-5D-5 L Health Questionnaire Quality of Life (QoL) functional outcome score [46, 48–50] over a period of 24 months. We will also aim to determine which method of treatment is associated with a higher incidence of complications as well as the time to union of malunion, nonunion and joint arthrosis. Lastly, we will determine whether initial displacement or quality of surgical reduction has an impact on functional outcome.

We hypothesize that there will be no statistically significant difference in functional outcomes between operative and nonoperative methods. We also hypothesize that there will be a greater incidence of complications in the operative group. Lastly, we hypothesize that fractures with a greater Neer classification and those with a greater degree of initial displacement will have worse functional outcomes.

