### Sub-analysis

In addition to the primary and secondary analyses outlined above, several other analyses are planned, though the study is not primarily powered for these statistical analyses. We will perform a subgroup analysis on the above outcome measures to assess whether there is a difference between 3- and 4- part proximal humerus fractures. This will primarily include a subgroup analysis of the Constant score, within groups of fracture type: 3- and 4- part fractures. The second will be a multivariable assessment of the progression of osteoarthritis between pre- and post-operative shoulders. A multivariable regression analysis will also be conducted of possible factors associated with progression of shoulder osteoarthritis, including demographic variables and fracture type. The third will be a multivariable regression analysis to determine which factors may be associated with functional outcome: with the Constant score as the dependent variable, demographic and radiographic factors (including osteoporosis) will be analyzed to determine if prognostic factors exist that may assist in planning treatment.

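### Secondary analysis C derives a treatment cut-off for displacement or angulation from a prognostic association, with no treatment interaction named

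*Protocol article*

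**What the plan says.** Secondary objective C asks a purely prognostic question: "Does the degree of initial displacement or angulation of the fracture fragments correlate with final functional outcome measures". The matching analysis (Secondary objective analysis, item C) is a multivariable regression with the Constant score as dependent variable and fracture angle and degree of displacement as the named independent variables. A second step follows, on condition that the regression shows an association: "area under the curve plots will be used to determine at what degree of angulation or displacement a particular treatment is indicated". Neither treatment nor an interaction with treatment is mentioned in item C's regression.

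The Purpose and hypothesis section states what the investigators expect. On treatment: "We hypothesize that there will be no statistically significant difference in functional outcomes between operative and nonoperative methods". On prognosis, they expect fractures of higher Neer class to do worse, and that "those with a greater degree of initial displacement will have worse functional outcomes".

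The end of the Discussion says the results will help surgeons choose the most effective treatment in the light of imaging findings, so a cut-off from item C would have a ready use.

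**The concern.** The condition concerns prognosis, while the conclusion concerns choice of treatment. If greater displacement lowers the Constant score by the same amount in both arms, the difference between the arms is the same at every displacement, and no degree of displacement favours one treatment more than another degree does. The rule as written would still go on to look for a cut-off.

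The area-under-the-curve step does not repair this. Such a plot shows how well displacement separates two outcome classes. However the 100-point Constant score is dichotomised, the plot distinguishes patients who end well from patients who end badly, not those who gain from fixation from those who do not.

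At stake is a published threshold, apparently backed by a randomised trial, that could steer patients towards or away from surgery without evidence that the treatment effect varies with displacement or angulation.

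**Working it through.** **What the rule tests and what an indication needs.** Let Y be the 24-month Constant score, T randomised treatment (0 or 1), D displacement and A angulation:

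Y = b0 + b1·T + b2·D + b3·A + b4·T·D + b5·T·A + error

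The treatment difference at given D and A is b1 + b4·D + b5·A. Item C's condition concerns b2 and b3 (or, with no interaction terms, slopes averaged over the arms). These do not appear in the treatment difference. Under the protocol's own hypotheses, taken with no interaction, b1 = b4 = b5 = 0 and b2 < 0: the condition can be met while the treatment difference is zero everywhere. Adding T as a plain covariate changes nothing, because the condition still concerns b2 and b3.

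**Inputs from the protocol (Sample size calculation).** Total 160, loss to follow-up 20%, SD 23.1, difference 12, alpha 0.05 (taken as two-sided), 80% power.
- The plan's own figure: 2 × (1.960 + 0.842)² × 23.1² / 12² = 58.2 per arm, against 58 stated. It reproduces and is not in dispute.
- Analysable patients: 160 × (1 − 0.20) = 128.

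**Assumed input.** The protocol gives no correlation r between displacement and the Constant score, so a range of 0.1 to 0.4 is shown (absolute value; the sign does not matter).

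**How often the condition is met with no treatment effect.** Using Fisher's z with one covariate, the standardised signal is atanh(r) × √(128 − 3), compared with 1.96:

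| r | atanh(r) | × √125 | chance of p < 0.05 |
|---|---|---|---|
| 0.1 | 0.1003 | 1.122 | 20% |
| 0.2 | 0.2027 | 2.267 | 62% |
| 0.3 | 0.3095 | 3.461 | 93% |
| 0.4 | 0.4236 | 4.737 | over 99% |

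A simulation with 128 patients, 1:1 allocation, a purely prognostic covariate, and no treatment effect or interaction agrees to within about a percentage point. In the same simulated trials a treatment-by-covariate interaction test was significant in about 5% at every r, its nominal rate.

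These are figures for one covariate. Item C names two, and if an association with either is enough, the condition would be met more often.

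**Precision of the correct analysis.** With 64 patients per arm, the standard error of the difference between the arms' slopes, per SD of displacement, is about 23.1 × √(2/64) = 4.08 points. The slope difference detectable with 80% power is about 2.80 × 4.08 = 11.4 points per SD, close to the 12-point minimum important difference. The correct analysis is feasible, but only as exploration.

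**The case against.** Several points on the other side are fair.

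- *The listed variables need not be the whole model.* Item C says multivariable, and treatment might be included. This stands as far as it goes: the text shows only that no interaction is named. But the condition for the cut-off would still be the covariate-outcome association.
- *The dichotomy needed for an area-under-the-curve plot may be in the full protocol or analysis plan.* This stands, so its absence is not counted as an error. The objection to the plot is that it answers a different question under any dichotomy.
- *The correlation may be low.* This also stands. Only displaced 3- and 4-part fractures are enrolled, which narrows the range of displacement. At r = 0.1 the condition is met in only about 20% of trials. That is why a range is shown, and why it would be too strong to say that the plan will produce an unsupported cut-off. The percentages count how often the condition is met, not how often a threshold is published.
- *Item C is one secondary analysis.* True, and this bears on severity.

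A reader might extend the criticism to the Sub-analysis section, which plans a "subgroup analysis of the Constant score, within groups of fracture type: 3- and 4- part fractures". The documents do not support that. No treatment indication is drawn from that analysis, the section says the study is not primarily powered for it, and no rule sets significance in one fracture type against non-significance in the other. An interaction test there may be left to the analysis plan. The same section's regression of prognostic factors, which "will be analyzed to determine if prognostic factors exist that may assist in planning treatment", is softer: it calls the factors prognostic and sets no cut-off.

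**Conclusion.** The concern holds for item C. It is an explicit rule, not a detail left to another document: a prognostic finding is turned into a statement of when a treatment is indicated. Under the protocol's own hypotheses, the condition can be met although treatment makes no difference at any displacement or angulation. The chance runs from about 20% to over 99% across assumed correlations of 0.1 to 0.4, against about 5% for an interaction test. This assumes 128 analysable patients, two-sided 0.05 and a single covariate. The direction of the conclusion does not depend on the correlation; only the frequency does.

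This should be fixed, but it is not critical. The primary comparison of Constant scores, the sample size and the randomisation are untouched.

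**What to change.** Keep the prognostic regression in item C as the answer to secondary objective C, and delete the area-under-the-curve treatment-indication step. Replace that step with:

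1. A regression of the 24-month Constant score on randomised treatment, continuous displacement, continuous angulation, and the interactions of treatment with each.
2. A plot of the estimated treatment difference, with its 95% confidence interval, across the observed range of displacement and of angulation.
3. A statement that this analysis is exploratory, and that no treatment indication will be given unless the interaction supports it.

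Reporting a treatment-by-fracture-type interaction with its confidence interval in the sub-analysis is an optional addition, not a correction.

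The cost is a change of wording before the analysis. Pre-operative CT for displacement and angulation is already planned in all patients. The drawback is that the interaction estimates will be imprecise, and the trial may be unable to say whether any threshold exists.
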